## Semi-structured interview

Participants (including dropouts) will complete a one-on-one semi-structured interview with a member of the research team approximately six weeks after completing the 12-week exercise program. Interviews will be conducted via Zoom and will be approximately 20 – 30 min in duration. All interview data will be recorded and transcribed verbatim, before being analyzed via inductive thematic analysis. The purpose of the interviews is to gain an understanding of the participants’ experiences during and following the 12-week exercise intervention. The interviews will explore the unique barriers and facilitators to exercise adherence that women with endometriosis experience, and they will also provide an opportunity for participants to provide feedback about the exercise program that may inform changes to exercise prescription in future research work involving women living with endometriosis. Data obtained from the interviews will provide critical information about key characteristics that make women well suited to undertaking an exercise program whilst living with endometriosis. Depending on the results, an a posteriori triangulation of the qualitative and quantitative data may provide enhanced insight into the potential benefits of exercise for women living with endometriosis.

## Safety and monitoring

Participants will be monitored through their allocated Garmin device, with the option to log pain reports, if an exacerbation occurs. The chief investigator (TH) will be notified of the report, to initiate follow-up. Participants are encouraged to work within the limits of their symptoms and have no assigned day to complete the exercise, allowing for flexibility in participation. Moreover, the EIS questionnaire asks participants to reflect on their symptoms across the last 7 days, providing additional monitoring.

Participants are asked to notify the team in the event of an exclusion factor or something that may prohibit continued participation (for example, pregnancy or any condition/illness that makes it unsafe to proceed), and the research team will then discuss discontinuation with the trial and the exit process.

In the event of symptom exacerbation, two members of the research team (TH & TM) will meet with the participant and attempt to provide modifications that alleviate symptoms but ensure the fidelity of the initial underlying exercise prescription remains unchanged.

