### Participants

Women (*n* *=* 50, assigned female at birth; AFAB; >18y) with medically diagnosed (imaging/ laparoscopy) endometriosis will be invited to participate. Recruitment will occur via various media outlets and will be ongoing in nature. Participants residing in the Australian Modified Monash Model (MMM) areas of MMM2-MMM7 will be invited to participate in the study. Participants must not be pregnant, breast-feeding or undergoing fertility treatment. Further, participants must not have had pelvic surgery, or an intrauterine device inserted or removed for the 6 months prior to beginning the study, and they must not have a diagnosis of adenomyosis. Moreover, participants who fail the 4-stage static balance test, are completing greater than 60 min of exercise per week or are currently using prescription steroids (prednisone or any derivative) will be excluded from the study.

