## Data analysis

All data will be de-identified for analysis and reporting. The estimated sample size was determined using data from Gonçalves et al.[25] where the mean difference for pain between the control and intervention was 24.74, for an effect size of d = 1.33 and comparisons between four groups, a sample size of 32 was estimated (alpha at 0.05 and power 0.80). Factoring in attrition and funding availability, the target sample size was set to 50. However, a piecewise (segmented) mixed-effect regression will be used to determine the critical threshold for exercise dose (primary outcome). Exercise dose (all randomized participants) will be determined by duration and intensity (heart rate) variables, aggregated weekly. For a sample of 50 participants across 12 weeks, with a mixed-effects piecewise model, there will be a minimum of 600 observations, which provide sufficient power and stability for this type of analysis[26]. Threshold and detectable change in slope will be determined by Y^t^ = B^0^ + B^1^* time^t^ + b^2^ * intervention^t^ + b^3^ time after intervention^t^ + e^t^, and confirmed with Davies Test. Intercurrent events such as medication changes, clinical exacerbations and poor adherence will be time- and date-stamped for consideration as co-variates in the regression analysis.

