All other data will be reported as mean ± standard deviation (SD) or median interquartile ranges. Normal distribution will be determined by Shapiro-Wilk’s test and non-normally distributed data will be logarithmically transformed prior to analysis. Pain, as a subset of the EHP-30 is the primary endpoint and will be analysed with an intention-to-treat analysis. A sensitivity (per-protocol analysis) will also be conducted to confirm outcomes. Secondary and exploratory endpoints will be arranged hierarchically as follows; quality of life (EHP-30), depression, stress, anxiety (DASS-21), functional capacity, sleep (PSQI), estradiol, CRP, cortisol. Multiple comparisons will be adjusted for using the Benjamini-Hochberg false discovery rate procedure. Missing data will be managed depending upon the volume of data, complete case analysis will be performed (<5%) for 5–40%, multiple imputation for chained equations or random forest imputation will be employed. Complier average causal effect (CACE) analysis will be employed if compliance varies significantly. Significance will be set at p < 0.05. All statistical procedures will be performed using Statistical Package for the Social Sciences (SPSS; Windows version 31.0, Chicago, IL, USA) and R Studio (2026.07.1).

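### An exclusion factor that arises after randomisation opens an exit from the trial, without separating stopping exercise from leaving follow-up, and this undermines the intention-to-treat analysis of pain

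*Protocol article*

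**What the plan says.** **The conduct rule.** Under Safety and monitoring: "Participants are asked to notify the team in the event of an exclusion factor or something that may prohibit continued participation". Pregnancy and an illness that makes it unsafe to go on are the examples given. The next step is that "the research team will then discuss discontinuation with the trial and the exit process". What may be discontinued is the trial. The section does not mention stopping the exercise while staying in follow-up. Symptom exacerbation has a separate route: two team members meet the woman and try to modify the programme.

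**The exclusion factors** (Participants) include:
- "Participants must not be pregnant, breast-feeding or undergoing fertility treatment"
- "participants must not have had pelvic surgery, or an intrauterine device inserted or removed for the 6 months prior to beginning the study"
- women who "are completing greater than 60 min of exercise per week or are currently using prescription steroids (prednisone or any derivative) will be excluded"

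**The endpoint and its analysis.** Survey data places the EHP-30 before and after the intervention only; the EIS is weekly. Data analysis says that EHP-30 pain "is the primary endpoint and will be analysed with an intention-to-treat analysis". Complete cases are used below 5% missing, and imputation from 5% to 40%.

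**Events after randomisation.** Data analysis also says: "Intercurrent events such as medication changes, clinical exacerbations and poor adherence will be time- and date-stamped for consideration as co-variates" in the regression.

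**Contact with women who leave.** "Participants (including dropouts) will complete a one-on-one semi-structured interview" about six weeks after the programme. No EHP-30 is mentioned for them.

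**The concern.** Intention-to-treat needs an outcome from every randomised woman, whatever happens to her exercise. A rule that moves from an event after randomisation straight to an exit from the trial produces missing endpoints that could have been collected. The EHP-30 has no intermediate measurement, so nothing on the pain scale itself stands in for the missing score.

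The loss may also be related to the outcome. The Background section names surgery among the most common treatments of endometriosis, and pelvic surgery is on the exclusion list. The exercise limit can also work differently by arm. At stake is a between-arm pain comparison with about 12 women per arm, where one or two missing scores matter. Pain scores that were never collected cannot be recovered by a later analysis plan.

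**Working it through.** **1. Inputs.**
- Design difference 24.74 and d = 1.33 (Data analysis). Implied SD = 24.74 / 1.33 = 18.6 points.
- Planned total before attrition: 32. This reproduces as a one-way ANOVA with four groups and f = 1.33 / 2 = 0.665. Eight per arm gives power 0.85; seven per arm gives 0.784. So the stated d and N fit together, and the implied SD is used below for illustration.
- Target 50 in four arms: 50 / 4 = 12.5. I assume 12 per arm.

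**2. When missing scores are not imputed.** 2 / 50 = 4%, below the 5% limit, so complete cases. 3 / 50 = 6%, so imputation. This reads the limit as the share of randomised women without a post-intervention pain score.

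**3. Worst-case shift in one arm.** Assume normal scores, and that the women who exit have the highest pain scores in their arm. The expected largest and second largest of 12 standard normal values are 1.629 and 1.116. Removing the k largest lowers the mean of the rest by (their sum) / (12 − k).
- k = 1: 1.629 / 11 = 0.148 SD; 0.148 × 18.6 = 2.8 points; 2.8 / 24.74 = 11%.
- k = 2: (1.629 + 1.116) / 10 = 0.274 SD; 0.274 × 18.6 = 5.1 points; 5.1 / 24.74 = 21%.

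**4. Effect on the comparison.** Simulation of two arms of 12 (40,000 replicates, SD 18.6, complete-case t-test at 0.05); difference = control minus exercise:

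| Highest scorers lost | Shift in difference | Rejection rate, true difference 24.74 | Rejection rate, no true effect |
|---|---|---|---|
| none | about 0 | 0.87 | 0.05 |
| 1 control | −2.8 | 0.80 | 0.07 |
| 2 control | −5.1 | 0.71 | 0.11 |
| 1 exercise | +2.8 | 0.94 | 0.08 |
| 2 exercise | +5.1 | 0.97 | 0.11 |
| 1 in each | about 0 | 0.90 | 0.07 |

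The sign depends on which arm loses the women. Equal losses leave the difference unbiased, though trimming both arms still lifts the rejection rate slightly when there is no effect.

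**5. The exclusion list beside the rest of the plan.**
- *Exercise volume.* The entry limit is 60 min per week. Exercise intervention prescribes yoga of 3 × 10 = 30 min plus walking. Short arm: 60 + 30 = 90 min, then 90 + 30 = 120. Long arm: 120 + 30 = 150 min, then 150 + 30 = 180. Both walking arms exceed the limit from the first week. Taken literally, every adherent walker has an exclusion factor; taken otherwise, the limit could apply only to the two control arms.
- *Steroids.* Starting a prescription steroid is an exclusion factor, which opens the exit discussion. It is also a medication change, which Data analysis treats as an event to be recorded and considered as a covariate. The article does not say which handling governs.
- *Surgery and intrauterine device.* The criterion looks back over the six months before study start, so whether it applies during the trial is unclear.

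**The case against.** The strongest reply is that exit is neither automatic nor aimed at women in pain. The text says that discontinuation is discussed, its examples are pregnancy and unsafe illness, and exacerbations lead to modification of the exercise. Recording a medication change and discussing continuation can both happen. Imputation is planned from 5% to 40% missing, and weekly EIS scores before exit could inform it. A condensed article may also leave follow-up after discontinuation to the full protocol.

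Much of this stands, and it rules out stronger readings that a reader might infer:
- *That several exclusion factors are treatments for uncontrolled pain.* Only surgery is named in the article as a treatment of the disease, and its criterion is a look-back. Nothing in the article links the intrauterine device or steroids to pain control.
- *That the analysis is no longer intention-to-treat.* All randomised women can still be analysed as allocated with imputed scores. The promise is weakened by avoidable missing outcomes, not abandoned.
- *That the trial loses its worst responders and the bias has a known direction.* The article gives no frequency or cause of exits, and the shift can go either way.

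The reply does not remove the rule as written. Exit from the trial is the only route stated once an exclusion factor arises. Imputation does not operate below 5% missing. Above that, standard imputation relies on exit being explained by recorded data. Silence on follow-up alone would be no finding, but a stated route out of the trial is.

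**Conclusion.** The point holds as a weakness in a stated conduct rule. An exclusion factor after randomisation leads to a discussion of leaving the trial, with no distinction from stopping exercise, and an early exit costs the primary pain score. This undermines the intention-to-treat analysis, most plainly when at most 2 of 50 scores are missing and none is imputed.

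The possible size is a shift of about 2.8 or 5.1 points for one or two women lost from a single arm. It is an upper illustration, not a forecast: it rests on 12 per arm, normal scores, an SD of 18.6, exits confined to one arm, and those women being exactly the highest scorers. Less selective or more balanced exits give less bias.

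Separately, the Participants, Exercise intervention, Safety and monitoring, and Data analysis sections do not agree on which exclusion factors count after randomisation.

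**What to change.** In Safety and monitoring, separate discontinuing the exercise programme from withdrawing from follow-up. State that the 12-week EHP-30, and the weekly EIS where the woman agrees, will be collected from every randomised woman unless she withdraws consent for data collection, and that pain will be analysed in all randomised women.

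Reconcile Participants, Exercise intervention, Safety and monitoring, and Data analysis on which exclusion factors apply after randomisation and how such events are recorded. Which events stop exercise remains for the investigators to decide.

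The cost is small: a change of wording and a little more survey follow-up. The baseline survey is online, the EIS runs through REDCap, and women who drop out are already to be contacted for interview. One downside is that scores after an event include the effect of any new treatment, which should be said when results are reported. The change should be made before any woman exits, because missed scores cannot be collected later.

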## Data analysis

All data will be de-identified for analysis and reporting. The estimated sample size was determined using data from Gonçalves et al.[25] where the mean difference for pain between the control and intervention was 24.74, for an effect size of d = 1.33 and comparisons between four groups, a sample size of 32 was estimated (alpha at 0.05 and power 0.80). Factoring in attrition and funding availability, the target sample size was set to 50. However, a piecewise (segmented) mixed-effect regression will be used to determine the critical threshold for exercise dose (primary outcome). Exercise dose (all randomized participants) will be determined by duration and intensity (heart rate) variables, aggregated weekly. For a sample of 50 participants across 12 weeks, with a mixed-effects piecewise model, there will be a minimum of 600 observations, which provide sufficient power and stability for this type of analysis[26]. Threshold and detectable change in slope will be determined by Y^t^ = B^0^ + B^1^* time^t^ + b^2^ * intervention^t^ + b^3^ time after intervention^t^ + e^t^, and confirmed with Davies Test. Intercurrent events such as medication changes, clinical exacerbations and poor adherence will be time- and date-stamped for consideration as co-variates in the regression analysis.

All other data will be reported as mean ± standard deviation (SD) or median interquartile ranges. Normal distribution will be determined by Shapiro-Wilk’s test and non-normally distributed data will be logarithmically transformed prior to analysis. Pain, as a subset of the EHP-30 is the primary endpoint and will be analysed with an intention-to-treat analysis. A sensitivity (per-protocol analysis) will also be conducted to confirm outcomes. Secondary and exploratory endpoints will be arranged hierarchically as follows; quality of life (EHP-30), depression, stress, anxiety (DASS-21), functional capacity, sleep (PSQI), estradiol, CRP, cortisol. Multiple comparisons will be adjusted for using the Benjamini-Hochberg false discovery rate procedure. Missing data will be managed depending upon the volume of data, complete case analysis will be performed (<5%) for 5–40%, multiple imputation for chained equations or random forest imputation will be employed. Complier average causal effect (CACE) analysis will be employed if compliance varies significantly. Significance will be set at p < 0.05. All statistical procedures will be performed using Statistical Package for the Social Sciences (SPSS; Windows version 31.0, Chicago, IL, USA) and R Studio (2026.07.1).

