## Description of protocol

### Study design

This study will adopt a prospective, parallel randomized controlled trial design and aligns with the Standard Protocol Items: Recommendations for Interventional Trials (SPIRIT) checklist. Participants will be required to provide written and verbal consent prior to involvement. Once enrolled into the study, participants will complete an online survey to ascertain demographic information, current treatment, management strategies, fertility and loss, perceptions of exercise, current exercise behaviours and preferences, and scores of depression, stress, anxiety, pain, sleep quality, and quality of life. Participants will then complete an initial telehealth consultation which will involve the assessment of functional capacity variables. Furthermore, measures of CRP, estradiol, and cortisol will be analyzed via a dried blood spot sample.

Participants will be provided with an activity monitor (Garmin Vivosmart 5) for activity tracking and monitoring of adherence, and a dried blood spot collection kit. Symptoms and engagement in exercise will be tracked weekly and following the completion of the intervention. Following the completion of the intervention, participants will complete a final telehealth appointment with the research team for assessment of functional capacity variables. Following the completion of the intervention (6 weeks after), participants will be invited to participate in a short (approximately 20 min) one-on-one semi-structured interview to ascertain their lived experience during and following the intervention (Table 1).

**Table 1 tbl0001:** Participant timeline: Schedule of enrolment, interventions, and assessments.

Adapted from Chan et al. [24],.

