### Survey data

Demographic information, current exercise behaviours (APSS), scores of depression, anxiety and stress (DASS-21), health-related quality of life (EHP-30), sleep (PSQI), self-efficacy (SEE) and open-ended questions regarding treatment, geographical location, fertility and access to care, will be collected pre- and post-intervention. Moreover, symptoms will be tracked weekly via the Endometriosis Impact Scale (EIS) through REDCap, a survey administration software program.

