## Limitations

This study is not without limitations. To address the spatial factors affecting endometriosis care, the mode of delivery is telehealth, as such this presents limitations with monitoring, adherence and attrition. As the exercise prescription is self-directed, adherence may be low, and attrition may result, and this may then reduce the power and observations. Moreover, the use of the activity monitor may vary depending upon user (logging physical activity), and therefore, some data may not be as reliable as laboratory-based data. Further, biomarker sampling, conducted via self-collected dried blood spots, was random and therefore not aligned with the menstrual cycle. Accordingly, data may not be indicative of maximal inflammatory and hormonal load associated with the condition and should be interpreted with caution. Finally, this study upheld strict exclusion criteria, so findings may not be applicable to individuals who present with comorbidities such as adenomyosis. To counter these limitations, future studies should consider fully supervised and individualized interventions.

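### The stated minimum of 600 observations is the complete-data maximum over 12 weeks, and this raw count does not demonstrate power for the threshold analysis

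*Protocol article*

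**What the plan says.** The Data analysis section of the protocol article labels the dose threshold the primary outcome and assigns it to a piecewise mixed-effects regression. Its only statement on power for that analysis begins "For a sample of 50 participants across 12 weeks, with a mixed-effects piecewise model" and continues "there will be a minimum of 600 observations, which provide sufficient power and stability for this type of analysis", with a citation as support.

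The record structure is one row per woman per week. On the exposure side, "Exercise dose (all randomized participants) will be determined by duration and intensity (heart rate) variables, aggregated weekly". On the outcome side, the Survey data section says "symptoms will be tracked weekly via the Endometriosis Impact Scale (EIS) through REDCap". The Study design section may add one later record: "Symptoms and engagement in exercise will be tracked weekly and following the completion of the intervention".

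On attrition, the Data analysis section says "Factoring in attrition and funding availability, the target sample size was set to 50", and the Limitations section says "attrition may result, and this may then reduce the power and observations". The Data analysis section also plans imputation when 5% to 40% of data are missing.

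The equation given for the threshold has an intercept, a time term, an intervention term, a time-after-intervention term and one error term. The result is to be determined from it "and confirmed with Davies Test".

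**The concern.** Two statements look wrong. First, a number that needs perfect follow-up is presented as a floor, in an article that elsewhere expects to lose observations. Second, a row count is offered as proof of power. Twelve weekly records from one woman are correlated, and the designed contrast in dose is mostly between women, so 600 rows are not 600 independent pieces of information on dose.

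A linked gap concerns the confirming test. The text names a mixed-effects model, but the equation as printed has no participant index, random effect, dose term or breakpoint. How the Davies test would allow for repeated measures is left open. The threshold is the trial's headline result, so both its power claim and its error rate matter.

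**Working it through.** **1. The plan's figure.** Inputs: 50 participants and 12 weeks (Data analysis), one record per participant-week (Data analysis, Survey data). 50 × 12 = 600, which reproduces the stated number exactly and uses every possible weekly record. Counting one post-programme record gives 50 × 13 = 650. Even then 600 is not guaranteed, because losing more than 50/650 = 7.7% of records falls below it.

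**2. What attrition does.** The article gives no rate, so these are assumed. If dropouts contribute nothing, the count is 600 × (1 − d). If dropout is spread evenly over the 12 weeks, it is 600 × (1 − d/2).

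| Assumed dropout d | Dropouts contribute nothing | Even dropout |
|---|---|---|
| 10% | 540 | 570 |
| 20% | 480 | 540 |
| 30% | 420 | 510 |
| 36% | 384 | 492 |

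The last row is the gap between the two sample sizes in the article, (50 − 32)/50 = 36%. It is not a stated dropout rate. At the upper end of the planned imputation range, 600 × (1 − 0.40) = 360 rows would be observed.

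**3. Where the dose contrast lies.** From the Exercise intervention section, prescribed weekly minutes (walking plus 3 × 10 of yoga) are 0, 30, 90 rising to 120, and 150 rising to 180. Arm means over the 12 weeks are 0, 30, 105 and 165, with overall mean 75 for equal arms.
- Between-woman variance: (75² + 45² + 30² + 90²)/4 = 4162.5.
- Within-woman variance: (0 + 0 + 15² + 15²)/4 = 112.5.
- Between-woman share: 4162.5/4275 = 97%.

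This is prescribed dose. The dose actually recorded will vary more within women.

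**4. Worst-case information.** If dose were constant within each woman, the effective number would be 600/(1 + 11 × ICC). The intraclass correlation (ICC) is assumed.
- ICC 0.3: 600/4.3 = 140.
- ICC 0.5: 600/6.5 = 92.
- ICC 0.7: 600/8.7 = 69.

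**5. Can the power claim be recomputed?** No. It gives no slope change, breakpoint, variance or ICC. The estimate of 32 (d = 1.33, alpha 0.05, power 0.80) is for a four-group comparison of pain and says nothing about a threshold. EHP-30 pain, named the primary endpoint, is collected only before and after the programme, at most 50 × 2 = 100 records, so the 600 can refer only to the weekly data.

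**6. The Davies test when no threshold exists.** Simulation of 50 women over 12 weeks with a random intercept, ten candidate breakpoints and 1000 runs per setting. Assumed dose was the prescribed minutes plus random variation between women and between weeks. Rejection rates at nominal 5%:

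| ICC | Dose breakpoint, clustering ignored | Time breakpoint, clustering ignored | Dose breakpoint, correlation modelled | Time breakpoint, correlation modelled |
|---|---|---|---|---|
| 0 | 4.4% | 4.5% | 4.3% | 4.0% |
| 0.3 | 29.4% | 1.3% | 3.5% | 4.1% |
| 0.5 | 43.2% | 0.3% | 5.4% | 4.5% |
| 0.7 | 49.8% | 0.0% | 3.9% | 5.2% |

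The modelled columns treat the covariance as known. A separate simulation (600 runs per ICC) with a dose breakpoint and clustering ignored gave 24%, 32% and 41% at ICC 0.3, 0.5 and 0.7.

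**The case against.** The strongest reply is that the plan does not ignore clustering. The sentence with the count names a mixed-effects model, which is built for repeated measures, and a condensed article may leave the random-effect structure and the details of the test to a fuller document. This stands. A reader might infer that the 600 rows will be analysed as 600 women, or that the analysis is invalid; the article says neither.

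A reader might also infer that the Davies test will produce false thresholds. That does not follow. Inflation needs a dose-axis breakpoint and ignored clustering together. The printed equation is written in time, and an unclustered test on that axis errs the other way (0% to 1.3% at ICC 0.3 to 0.7). Nor does the test rest on the count of 600.

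The effective numbers in step 4 are a worst case. The analysis uses recorded weekly duration and heart rate, which vary within women, and a mixed model uses that variation. Passive controls are not wasted rows either, since they log incidental exercise and anchor the low end of dose.

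Finally, 32 is not an expected number of completers, so 384 rows is not the plan's expectation. It also assumes that dropouts contribute nothing, whereas a mixed model keeps their earlier weeks.

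None of this rescues the word minimum. Nor does naming a mixed model turn a row count into a power calculation. The Limitations section does disclose that observations may be lost, but that contradicts the claimed floor and does not repair it.

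**Conclusion.** The point holds in two parts, with a third that is conditional.

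- The direction of the stated figure is wrong: 600 is the complete-data maximum over 12 weekly records (650 with one more). This is arithmetic from the article's own numbers.
- Power for the threshold analysis is not demonstrated, because the only support in the text is a raw count and a citation. The article does not show that power is inadequate, and that stronger reading should not be drawn. The range of 140 to 69 effective observations rests on assumed ICCs and on dose varying only between women.
- The printed equation does not secure the error rate of the confirming test. The roughly 24% to 50% false-positive rate applies only to a dose breakpoint with clustering ignored, under assumed ICCs and dose distributions. With the correlation modelled, the rate was 3.5% to 5.4%.

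**What to change.** In the Data analysis section:

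1. Replace the minimum with *up to 600 weekly observations from 50 participants, fewer with attrition*, and give the expected number under a stated attrition rate. If the post-programme record enters the model, state the ceiling as 650.
2. Delete the claim of sufficient power and stability, or replace it with a simulation of the mixed segmented model under a stated slope change, breakpoint, residual variance, ICC and attrition rate.
3. Write the model with a participant index and random effects, weekly dose, and an explicit breakpoint in dose.
4. Specify a threshold test that respects clustering by participant, for example a parametric or participant-level bootstrap, or say how the Davies test will be fitted to the mixed model.

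The cost is wording, some computing time and a less favourable stated figure. The changes should be made before outcome data are seen.
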